##### Clinical data

For each house, the mean Hb will be calculated and these means compared between each intervention group and the control group using ANOVA.

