## Methods

### Study area, house- and participant eligibility

The study area is situated approximately 170 km from the mouth of the Gambia River and covers 70 km^2 ^of the North Bank Division in The Gambia, an area of open Sudan savanna vegetation. The climate consists of a single rainy season from June to October followed by a long dry season. Specifically, the study area comprises 500 houses; 46 in 11 residential blocks in Farafenni town (UTM coordinates: 1500200N, 435500E) and 454 in 25 villages located within 15 km of the town. Farafenni itself is a market town with a population of over 20,000 inhabitants, situated less than 5 km from the river and 2 km south of the border with Senegal. Houses in both the town and surrounding villages are usually arranged in familial compounds demarcated by a fence or wall, though there are some in which the houses are rented by unrelated family groups. Compounds in Farafenni contain typically 1–4 houses and in the villages 4–6 houses, but sometimes as many as 20. Houses must meet 6 eligibility criteria in order to be selected: (1) they must be single storey buildings, (2) have open eaves, (3) with no more than four rooms, (4) have no existing ceilings, (5) have no screening and (6) at least one child, aged 6 months to 10 years, must sleep in the house at night. Most of the houses to choose from are part of the Farafenni demographic surveillance system (FDSS) that incorporates 46 residential blocks in the town and 23 surrounding villages, also defined as individual blocks within the FDSS.

The study area population comprises 7852 people dominated by three ethnic groups; Mandinka (28%), Wollof (38%) and Fula (27%). There are roughly equal numbers of men (53%) and women. The study aims to recruit 1250 children aged 6 months to 10 years, as this is the age group most affected by the clinical manifestations of malaria. No distinctions are made regarding gender or ethnic group. Moreover, as the target population will in reality be all children occupying study houses, and in order for the results from this study to be broadly applicable, no distinctions are made in terms of medical condition or physical health.

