#### b) Clinical

Our aim was to have 90% power to detect a difference in mean haemoglobin of 0.5 g/dl between the two intervention arms and the control arm in November, using a significance level of 2.5% for each of the two comparisons of intervention with control. In a recent trial in The Gambia the SD was 1.7 g/dl. A difference of 0.5 g/dl is 0.3SD. The interclass correlation (ICC) for haemoglobin in another trial in Senegal varied from 0.04 to 0.08. Assuming a similar ICC in the present trial the number of children required to detect (with 90% power) a difference of 0.5 g/dl is 166 in the control arm and 332 in each intervention arm.

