##### Clinical data

The secondary analysis will be done adjusting for the same variables as the primary analysis but including all the covariates listed in the entomological analysis, with three changes: (1) whether the study subject reports sleeping under an ITN (rather than whether someone in the trapping room uses an ITN as in the entomological analysis), (2) whether the net was in good condition or not. A net in good condition is one which is long enough to be tucked under the mattress, is not torn or otherwise damaged, and had no more than 5 small holes (finger-width, approximate diameter ≤ 2 cm [15], (3) child's age. Interactions with age will be investigated using age groups: under 2 years old, 2–5 years, and 5–10 years old.

For the clinical variables (haemoglobin, anaemia, severe anaemia, parasitaemia, high density parasitaemia and parasite density in infected children), generalized estimating equations (GEE) will be used to estimate the odds ratios between each intervention group and the control group.

Comparisons of clinical variables (haemoglobin, anaemia, severe anaemia, parasitaemia, high density parasitaemia and parasite density in infected children) between intervention groups will be reported as the difference in risk or the difference between means, with 95% confidence intervals.

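### The primary haemoglobin analysis weights every house equally and leaves out the child's age: valid, but it loses information, by an amount that depends on house sizes the protocol does not give

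*Protocol article*

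**What the plan says.** The clinical paragraph under Analysis, d) Primary analysis of variables, is one sentence: "For each house, the mean Hb will be calculated and these means compared between each intervention group and the control group using ANOVA". It mentions neither weights nor age. Analysis b), on the ITT and ATP sets, adds year, rural/urban location and block to the analyses. It declines to adjust for the number of children, on the ground that this number should be unrelated to the clinical outcomes.

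Age comes in only under e) Secondary analysis, as "3) child's age. Interactions with age will be investigated". The GEE for the clinical variables, haemoglobin included, is also secondary.

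On house size, the eligibility section requires that "at least one child, aged 6 months to 10 years, must sleep in the house at night". It plans 1250 children, and the Design section plans 500 houses. The number of children per house is a stratification factor in the randomisation.

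The clinical sample size is counted in children. Its target is stated as "Our aim was to have 90% power to detect a difference in mean haemoglobin of 0.5 g/dl", with testing at 2.5% for each comparison with control. For the spread of haemoglobin it borrows a figure from outside: "In a recent trial in The Gambia the SD was 1.7 g/dl". For clustering it relies on a different study: "The interclass correlation (ICC) for haemoglobin in another trial in Senegal varied from 0.04 to 0.08".

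**The concern.** With an ICC of 0.04 to 0.08, at least 92% of the haemoglobin variance lies between children in the same house. The precision of a house mean therefore depends mainly on how many children it averages. Relative to a single child, the variance of a five-child mean is (1 + 4 × ICC)/5, which is 0.232 at ICC 0.04 and 0.264 at ICC 0.08. A one-child mean thus has 3.8 to 4.3 times the variance of a five-child mean, yet both count the same in the planned ANOVA.

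Age may matter for the same reason. The children range from 6 months to 10 years, and the Discussion explains that haemoglobin is deliberately not measured at the start of the season. Age is therefore one of the few child-level variables that could sharpen the comparison, and the primary analysis does not use it.

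At stake is the precision of the main clinical comparison, in a design that has little power to spare.

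**Working it through.** **Inputs from the protocol.** Difference 0.5 g/dl; SD 1.7 g/dl; ICC 0.04–0.08; 2.5% level per comparison (sidedness not stated, taken as two-sided); 100 control and 200 houses per intervention arm, or 90 and 180 after the 10% allowance in the entomological sample size section; mean house size 1250/500 = 2.5, so about 250 control children and 500 per intervention arm.

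**Assumption.** The distribution of children per house, m, is not given. Several shapes with mean 2.5 are tried.

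**1. The plan's own figure.** The protocol states that the number required for "a difference of 0.5 g/dl is 166 in the control arm and 332 in each intervention arm". Control children before clustering, at 1:2 allocation: (2.241 + 1.282)² × (1.7/0.5)² × (1 + 1/2) = 12.41 × 11.56 × 1.5 ≈ 216, with 432 in the intervention arm. Using the rounded 0.3 SD gives 207 and 414. Multiplying by 1 + 1.5 × ICC (1.06 to 1.12) gives about 229–242 control children (220–232 with 0.3 SD). So 166/332 is not reproduced. At 166/332, power is about 80% without clustering and 75–78% with it. This shortfall exists whatever the analysis.

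**2. Variance per house.**
- Equal weights: SD² × [ICC + (1 − ICC) × E(1/m)].
- Optimal weights: SD² / E[m/(1 + (m − 1) × ICC)].
- Information kept by equal weights: the second divided by the first.

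**3. Worked case: zero-truncated Poisson, mean 2.5, E(1/m) = 0.539.**
- ICC 0.04: equal weights 0.04 + 0.96 × 0.539 = 0.558; optimal 1/2.302 = 0.434; ratio 0.779.
- ICC 0.08: equal weights 0.08 + 0.92 × 0.539 = 0.576; optimal 1/2.142 = 0.467; ratio 0.810.

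SE of the difference = 1.7 × √(variance factor) × √(1/100 + 1/200). At ICC 0.04 this is 0.1555 with equal weights and 0.1372 with optimal weights. Power = Φ(0.5/SE − 2.241) = 83.5% and 92.0%. At ICC 0.08 it is 82.2% and 89.9%.

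**4. Range over assumed house sizes** (first value ICC 0.04, second ICC 0.08; power as equal v optimal weights)

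| Children per house | Information lost | Power, 100 v 200 houses | Power, 90 v 180 houses |
|---|---|---|---|
| Half 2, half 3 | about 3% | 91.6, 90.1% v 92.5, 90.9% | 88.4, 86.6% v 89.5, 87.5% |
| 1/2/3/4 in 10/40/40/10% | 11, 9% | 89.0, 87.5% v 92.4, 90.6% | 85.2, 83.5% v 89.3, 87.2% |
| Uniform 1–4 | 20, 17% | 84.8, 83.4% v 92.1, 90.2% | 80.5, 79.0% v 89.0, 86.7% |
| Zero-truncated Poisson | 22, 19% | 83.5, 82.2% v 92.0, 89.9% | 79.1, 77.6% v 88.8, 86.3% |
| Geometric | 29, 25% | 78.6, 77.5% v 91.3, 88.8% | 73.8, 72.6% v 88.0, 85.0% |

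**5. Higher ICC.** With the zero-truncated Poisson, an ICC of 0.15 gives a loss of about 15% and an ICC of 0.30 about 8%.

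**6. Age.** Adjustment multiplies the SE by about √(1 − R²), where R² is the share of haemoglobin variance explained by age. The protocol gives no R². Purely for illustration, an assumed 5% gives 0.975 and 15% gives 0.922. None of this is included in the table.

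**The case against.** **Nothing here is invalid.** House means are a standard analysis at the unit that is randomised, and they match the per-house entomological ANOVA. Stratifying on the number of children should keep house sizes similar across arms. This stands: the fault is efficiency, not bias.

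**The loss rests on an assumption.** A reader might infer a definite loss of about a fifth. The protocol fixes only a minimum of one child, a mean of 2.5 and the fact that sizes vary. If nearly all houses hold two or three children, the loss is about 3% and the planned ANOVA still gives 90–92% power with no house loss. This stands. On the other side, only children sampled in November are analysed, and the Discussion describes a mobile population whose children are often sent away. Absences will reduce some houses to a single child, so the near-equal case is not the one to rely on.

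**The power shortfall has other causes.** A reader might blame this analysis for missing 90%. In every case tabulated, optimal weights also fall below 90% after the 10% loss of houses, and the 166/332 calculation falls short on its own inputs. It is also fair to say that the planned 250 control children exceed the stated 166 even after a 22% loss (250 × 0.78 = 195). That comfort depends on the 166, however, and the protocol's inputs call for about 229–242.

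**The ICC may not apply to houses.** The protocol does not say what the cluster was in the trial it cites. A higher ICC shrinks the weighting loss, but lowers power under every analysis.

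**Age.** A reader might take an age imbalance as bias. Chance imbalance after randomisation is not bias, and the confidence interval allows for it. The secondary analysis already adjusts for age. The case for moving it into the primary analysis is precision alone.

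**Conclusion.** The point holds as one of efficiency. Equal weighting loses about 3% to 29% of the information at the protocol's own ICC, and 19–22% under a zero-truncated Poisson; which figure applies depends on unreported house sizes. In the Poisson case, optimal weights raise power from about 82–84% to 90–92% with all houses, and from about 78–79% to 86–89% after the 10% loss. That recovers much of the power but is no guarantee of 90%, and the clinical sample size calculation is a separate shortfall to correct in its own right. The gain from adding age cannot be quantified from the protocol. The results assume an SD of 1.7 g/dl, a two-sided 2.5% test, a normal approximation, the same house-size distribution in each arm and every listed child sampled. The change is worth making because it costs so little, not because the planned analysis is wrong.

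**What to change.** Make one of these the primary haemoglobin analysis:
- a child-level linear mixed model with a random house effect;
- a GEE clustered on house with exchangeable correlation and an identity link, so that the effect is in g/dl;
- ANOVA on house means weighted by m/(1 + (m − 1) × ICC), where m is the number of children sampled and the source of the ICC is prespecified.

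Adjust for year, rural/urban location and block, as already planned, and for child age in a prespecified form. Keep the unweighted house-mean ANOVA as a sensitivity analysis. If the numbers of children per listed house are available, state their distribution, so that the loss can be computed rather than assumed.

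The cost is wording: individual haemoglobin values and ages are already to be recorded, and a GEE is already planned as secondary. The one real downside is that the effect becomes closer to an average over children than over houses. Under the protocol's own premise that the number of children is unrelated to the clinical outcomes, the two are the same, and the sensitivity analysis would show if they were not. Weighting does not conflict with the decision not to adjust for the number of children, since it changes precision and adds no covariate.

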#### e) Secondary analysis

##### Entomological data

The secondary analysis will impute missing mosquito catch data for nights when individual houses could not be sampled. The analysis will be done adjusting for the same variables as the primary analysis but including the following covariates that have been shown to be associated with mosquito catch size[14]: (1) presence of horse(s) tethered near the house at night, (2) churai burnt in the trapping room at night, (3) number of people sleeping in the trapping room at night, (4) wall material (mud brick or concrete).

Night-to-night variation in covariates 1, 2 and 3 can be accounted for as these will be recorded on every visit to each house. Covariate 4 will obviously remain constant throughout the trapping period for each house. We will also include the presence of one or more ITNs in the house, and socioeconomic status, in the list of covariates. Socioeconomic status will be determined by principal component analysis (PCA) from a list of household assets.

Generalised estimating equations (GEE) will be used to estimate treatment effect, adjusting for covariates. Differences in house entry by malaria mosquitoes experienced in the three groups will be analysed based on count data, using a generalised estimating equation to account for the correlation between the longitudinal observations in the same house comparing the number of mosquitoes caught indoors in each house in each intervention group with the control group.

##### Clinical data

The secondary analysis will be done adjusting for the same variables as the primary analysis but including all the covariates listed in the entomological analysis, with three changes: (1) whether the study subject reports sleeping under an ITN (rather than whether someone in the trapping room uses an ITN as in the entomological analysis), (2) whether the net was in good condition or not. A net in good condition is one which is long enough to be tucked under the mattress, is not torn or otherwise damaged, and had no more than 5 small holes (finger-width, approximate diameter ≤ 2 cm [15], (3) child's age. Interactions with age will be investigated using age groups: under 2 years old, 2–5 years, and 5–10 years old.

For the clinical variables (haemoglobin, anaemia, severe anaemia, parasitaemia, high density parasitaemia and parasite density in infected children), generalized estimating equations (GEE) will be used to estimate the odds ratios between each intervention group and the control group.

Comparisons of clinical variables (haemoglobin, anaemia, severe anaemia, parasitaemia, high density parasitaemia and parasite density in infected children) between intervention groups will be reported as the difference in risk or the difference between means, with 95% confidence intervals.

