#### b) Intention to treat (ITT) and according to protocol (ATP) analysis sets

The analysis of primary and secondary endpoints will be considered two ways. Firstly we will adopt an 'intention to treat' approach where the analysis is carried out using all households that are randomized and for which there are some outcome data. At enrolment of the house, a list of children who normally sleep in the house will be made and updated at the beginning of the rainy season to include newborns and record any changes in occupancy. At blood sampling in November, any children absent will be listed with the reason they were missing. The ITT study population for the anaemia endpoints is all children included in the updated list. Analysis will be limited to those who were sampled for Hb and parasitology in November.

Secondly, we will adopt an 'according to protocol' approach where the analysis is carried out using all houses and study subjects in the control group, but excluding all houses from either intervention group (and study children that slept there) that have screening scored as 'badly damaged' in a durability study conducted 6 months post screening installation. The definition of 'badly damaged' screens will be determined separately for homes in the two treatment arms. In full screened houses damage will equate to 5 or more holes in the screening and/or doors not closing tightly. In screened ceiling houses damage will equate to 5 or more holes in the screening and/or where the netting has come away from the battens that secure the screening to the walls.

ITT and ATP analyses will include stratification by year, by rural/urban, and by block, which were stratification factors in the randomization. There will be no adjustment for the number of children in each trial arm even though this was a stratification factor in the randomization. We stratified to ensure similar numbers in each trial arm for Hb sampling, but the number of children in the house is not expected to relate to any of the clinical outcome measures.

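### The secondary clinical analysis names odds ratios versus control for haemoglobin and for parasite density in infected children, which are continuous, so the effect measure is wrong for these two outcomes

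*Protocol article*

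**What the plan says.** The clinical part of the secondary analysis (Protocol article, Analysis, e) Secondary analysis, Clinical data) has three steps.

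- **Covariates.** "The secondary analysis will be done adjusting for the same variables as the primary analysis but including all the covariates listed in the entomological analysis". Three changes to that list follow: the child's own use of a treated net, the condition of the net, and the child's age.
- **Comparison with control.** "For the clinical variables (haemoglobin, anaemia, severe anaemia, parasitaemia, high density parasitaemia and parasite density in infected children"; for this whole list, "generalized estimating equations (GEE) will be used to estimate the odds ratios between each intervention group and the control group".
- **A further comparison.** The same six variables are listed again, and comparisons "between intervention groups will be reported as the difference in risk or the difference between means, with 95% confidence intervals".

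Three other places bear on haemoglobin versus control.

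- **Primary clinical analysis (Analysis, d), Clinical data):** "For each house, the mean Hb will be calculated and these means compared between each intervention group and the control group using ANOVA".
- **Analysis sets (Analysis, b)):** "ITT and ATP analyses will include stratification by year, by rural/urban, and by block".
- **Sample Size Rationale, b) Clinical:** the aim is "90% power to detect a difference in mean haemoglobin of 0.5 g/dl between the two intervention arms and the control arm in November". The same sentence fixes the test level for these contrasts: "using a significance level of 2.5% for each of the two comparisons of intervention with control".

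**The concern.** An odds ratio compares the odds of an event. Haemoglobin in g/dL and parasite density per μL are measurements, not events, so an analyst who follows the sentence literally has no defined quantity to estimate for them.

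Haemoglobin is the variable on which the clinical sample size rests, and that calculation is framed as a difference in means. The secondary analysis is where the child's age, the child's net use and the net's condition enter. It is therefore the natural check on whether the haemoglobin result is robust to those factors. The article's Discussion explains that anaemia is not measured at the start of the rainy season and that comparability rests on randomisation, which makes such a check more useful.

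If the scale of the adjusted effect is misnamed, the adjusted and primary haemoglobin results may not be comparable, and the scale could be chosen once the data are in hand.

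**Working it through.** No figure in the plan bears on this point and no arithmetic applies. The check sets the passages side by side.

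**Step 1. Classify the six variables.** The Design section defines anaemia as Hb below 8 g/dL, severe anaemia as Hb below 5 g/dL, and high parasite prevalence as 5000 parasites/μl or more.

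| Variable in the secondary clinical list | Type | Does an odds ratio versus control fit? |
|---|---|---|
| Haemoglobin | continuous | no |
| Anaemia | binary | yes |
| Severe anaemia | binary | yes |
| Parasitaemia | binary | yes |
| High density parasitaemia | binary | yes |
| Parasite density in infected children | continuous | no |

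**Step 2. Could the two continuous items be meant in cut form?** The cut forms of haemoglobin (anaemia and severe anaemia) and of parasite density (high density parasitaemia) are already separate entries. Cutting the continuous items again would duplicate those entries. No cut point or ordinal model is given for them. The natural reading is that both are to be analysed as continuous, and the named effect measure does not suit that.

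**Step 3. Does the next sentence repair it?** It offers a difference in risk or in means, which would suit the outcome types. The question is which arms it compares.

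- *Narrow reading: the two screening arms.* The sentence just before it names the control group explicitly when control is meant; this one does not. The primary entomological analysis sets 97.5% intervals for comparisons with control and a 95% interval for the comparison of the two screening arms. The 95% in this sentence matches the latter. On this reading, haemoglobin and parasite density versus control are left with the odds ratio alone.
- *Wide reading: all trial arms.* The primary entomological text specifies two groups when it compares the screening arms, and this sentence does not, so it might cover every comparison. On this reading, haemoglobin versus control has two effect measures in adjacent sentences, an odds ratio and a mean difference, and the first is still undefined.

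Neither reading leaves the text correct as it stands.

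**Step 4. What else covers these outcomes versus control?** For haemoglobin, the primary analysis compares house means by ANOVA, with stratification by year, rural/urban location and block. That is on the mean scale and agrees with the 0.5 g/dl used for sample size. The defect does not touch it. For parasite density, the primary clinical analysis names no comparison, so the secondary sentence is the only one in the article that expressly compares it with control.

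**The case against.** The best defence is that odds ratios is loose shorthand over a list in which four of six items are binary. A GEE with an identity link is routine for a continuous outcome, the parallel entomological GEE speaks neutrally of a treatment effect, and the sentence on differences between means shows that the authors knew which variables need means. Link functions and transformations are also details that an article can leave to a fuller analysis plan.

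Much of this stands. It shows that the intention was probably sound and that the slip is easy to correct. It does not make the sentence right: the article does not leave the effect measure open but names one, and for two outcomes it is the wrong one.

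The objection also disposes of three stronger readings that a reader might infer.

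- *That no valid adjusted effect on haemoglobin versus control is planned.* The documents do not support this. The primary ANOVA gives a mean comparison with control that takes account of the stratification factors, and the secondary section does plan a covariate-adjusted GEE that includes haemoglobin. Only the measure it is said to produce is wrong.
- *That the plan forces haemoglobin to be dichotomised, with a loss of information.* The plan nowhere says this, and the separate listing of the anaemia outcomes points the other way. A figure for the loss would also need a mean haemoglobin that the article does not give.
- *That the 95% level is itself an error.* The 2.5% level is set for the powered clinical comparisons, and the 97.5% interval for the primary entomological ones. Nothing extends either to this secondary estimate.

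**Conclusion.** The point holds in a limited form. For two of the six clinical variables, haemoglobin and parasite density in infected children, the effect measure stated for the covariate-adjusted secondary comparison with control is wrong and cannot be followed as written. The next sentence does not clearly repair this, because it reads as a comparison of the two screening arms or, at best, is ambiguous.

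The consequence is confined to the secondary analysis. The primary haemoglobin comparison, its stratification and the power calculation are not affected, and the odds ratio is suitable for the four binary outcomes.

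The conclusion assumes that the two items are meant as continuous measures, which their separate listing from the cut versions supports. It does not depend on which reading of the following sentence is taken.

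**What to change.** Replace the single effect measure with one for each outcome type. For each intervention versus control:

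- **Haemoglobin:** GEE with identity link, reported as an adjusted difference in means.
- **Parasite density in infected children:** GEE on the log scale, reported as an adjusted ratio of geometric means.
- **Anaemia, severe anaemia, parasitaemia, high density parasitaemia:** GEE with logit link, reported as adjusted odds ratios.

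Then state whether the following sentence compares only the two screening arms or all arms. If it is meant to cover control as well, reconcile it with the measures above so that each comparison has one named lead measure.

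A 97.5% interval for the comparisons with control would be consistent with the 2.5% level in the clinical sample size and with the primary entomological intervals, but it is optional here.

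The cost is a rewording of the two sentences. Data collection, sample size and the GEE method stay the same.
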